## Abstract

**Background:**

Home care service providers are increasingly supporting clients living with dementia. Targeted and comprehensive dementia-specific training for home care staff is necessary to meet this need. This study evaluates a training programme delivered to care staff (paid personal carers) of clients living with dementia at home.

**Methods:**

This study is a pragmatic stepped-wedge cluster-randomised controlled trial (SW-CRT). Home care workers (HCWs) from seven home care service providers are grouped into 18 geographical clusters. Clusters are randomly assigned to intervention or control groups. The intervention group receives 7 h of a dementia education and upskilling programme (Promoting Independence Through quality dementia Care at Home [PITCH]) after baseline measures. The control group receives PITCH training 6 months after baseline measures. This approach will ensure that all participants are offered the program. Home care clients living with dementia are also invited to participate, as well as their family carers. The primary outcome measure is HCWs’ sense of competence in dementia care provision.

**Discussion:**

Upskilling home care staff is needed to support the increasing numbers of people living with dementia who choose to remain at home. This study uses a stepped-wedge cluster-randomised trial to evaluate a training programme (PITCH) for dementia care that is delivered to front-line HCWs.

**Trial registration:**

anzctr.org.au; ACTRN12619000251123. Registered on 20 February 2019.

## Background

Most older Australians would rather live at home than in residential aged care [1], to maintain independence and autonomy [2] and retain connections to their social networks of friends, family, and community [3]. Likewise, a significant number of people living with dementia live at home (approx. 56%), either alone (8%) or with others (48%) (AIHW Survey of Disability, Ageing and Carers (2018)) [4]. As of 2019, 9% of people using home care in Australia were receiving the Dementia and Cognition Supplement (approximately 10,000 clients), though this number does not represent the prevalence of dementia in home care as this additional funding is only for recipients living with moderate to severe dementia [5].

It is crucial that home care workers (HCWs) are able to deliver high quality dementia care for clients living at home. However, this workforce is often not provided with the necessary specialist dementia training and education, with a recent systematic review demonstrating a dearth of evidence surrounding interventions aimed at improving the quality of home care for people living with dementia [6]. This finding raises concerns, as home care directly influences the quality of life of people living with dementia and their ability to remain independent and safe, particularly as their symptoms progress [7]. Providing home care also poses unique challenges, as HCWs, unlike residential aged care staff, work alone with little direct supervision in the client’s home meaning there are fewer opportunities to learn from others in their workplace. Therefore, it is fundamental there is adequate training to help HCWs nurture the higher-level skillset and situational adaptability necessary for providing good dementia home care [8].

Remaining at home offers more autonomy for people living with dementia and costs less compared to residential aged care and acute health care [9]. For these reasons, the Australian Government subsidises long-term home care (such as the Home Care Package Program and the Commonwealth Home Support Programme), including additional support for people with moderate to severe cognitive impairment via the dementia and cognition supplements. The home-based care services provided include personal care (i.e. assistance with bathing, toileting, dressing), domestic tasks (meal preparation, washing, ironing, and cleaning), transport, home maintenance, feeding pets, social support, and gardening. As HCWs have ongoing interaction with clients living with dementia, they often play an important role in the clients’ psychological, intellectual, emotional, and social needs and advocate for them, such as, reporting signs of abuse or neglect to case managers. Additionally, family carers may also benefit from respite during the HCW visit. Good quality targeted home care helps reduce hospital admissions, delays institutionalisations, and improves quality of life [10].

The growing need for dementia home care services warrants well-trained, highly skilled, empathetic home care support staff, who can deliver quality, person-centred care. Therefore, HCWs need dementia training and supervision on topics including [8]: enhancing well-being, managing neuropsychiatric symptoms and changed behaviours, prevention and management of suspected neglect and abuse, promotion and maintenance of client independence, and communication skills. The Clinical Practice Guidelines and Principles of Care for People with Dementia [8] recommend a multi-factorial and multi-session training programme to improve dementia care. Many home care workers may have undertaken short-course vocational training (such as a Certificate 3 in Aged Care), but the dementia component of this training varies greatly and is typically limited [11]. Therefore, many home support workers have very limited dementia specialist training and knowledge [12]. The recent Royal Commission into Aged Care Quality and Safety (Royal Commission) found serious shortcoming in the quality of aged care for older Australians [13] and also identified the need for specialist dementia care training for aged care workers, including home care workers (ref). The Clinical Practice Guidelines also stress the importance of evaluating the impact of educational programs on staff practices and outcomes for people living with dementia, carers, and families [8].

To address these gaps in knowledge, the Promoting Independence Through quality dementia Care at Home (PITCH) programme was developed to provide an education and training package specifically targeted to home care workers. This programme has been co-designed with HCWs and managers, people living with dementia, and their family carers. We are undertaking a pragmatic stepped-wedge cluster-randomised trial (SW-CRT) to evaluate the PITCH programme [14]. The aim of the trial is to determine the efficacy and feasibility of implementing the specialist dementia training programme to HCWs to improve their confidence and knowledge when servicing clients living with dementia, as well as evaluate clinical and health outcomes for clients and family carers. A stepped-wedge trial was chosen to facilitate the logistics of rolling out the intervention: the lead organisation is conducting the training, and there are significant lead-in times to coordinate workforce training across multiple partner home care providers that are geographically dispersed within and across states. This design was also chosen to minimise contamination, to increase statistical efficiency, as well as improve the likelihood of home care provider participation and ongoing engagement.

This study will address the following research questions:
Is PITCH effective in improving the skill-set of HCWs?Will improving the skill-set of HCWs trained in PITCH indirectly improve health and care outcomes for clients and family carers?Is PITCH cost effective compared with usual care practice?

In this SW-CRT, we hypothesise the following:
PITCH-trained HCWs will have an improved sense of competence in providing care, improved dementia knowledge, and reduced carer burden at 6 months, compared with HCWs not trained in PITCH.Clients of PITCH-trained HCWs will report a better experience with their home care service, improved quality of life and health, and exhibit fewer behaviours of concern at 6 months, compared with clients of HCWs not trained in PITCH.Family carers of clients of PITCH-trained HCWs will have reduced carer burden and reduced depressive symptoms at 6 months, compared with family carers of clients with HCWs not trained in PITCH.Clients with usual care will have fewer total days before an all-cause transition from the home event (such as admission to residential care) or greater client total number of transitions from home to hospital or other facilities, compared with clients of PITCH-trained HCWs.PITCH is effective compared to control in terms of quality-adjusted life years as measured by economic evaluation.

## Methods/design

### Trial design

This pragmatic stepped-wedge cluster-randomised controlled trial (SW-CRT) investigates the effectiveness of the PITCH training programme delivered to paid HCWs in improving their competency and dementia knowledge, overall family carers’ wellbeing and clients’ quality of life, and cost-effectiveness. The study participants are clients living with dementia, family carers, and HCWs.

Consistent with the stepped-wedge design, clusters of participants undertake PITCH training (the intervention) sequentially over time and, once their training is completed, will remain exposed to the intervention for the duration of the study. Every cluster begins in the control condition and eventually receives the intervention, with crossover determined randomly, ensuring eventual participation of all groups for ethical reasons. The study is conducted at six home care service providers, with each provider potentially contributing more than one cluster.

This SW-CRT is an interventional study for HCWs as they receive PITCH training, but a non-interventional study for the clients and family carers (no direct intervention treatment is given to clients). HCWs are randomly allocated to either the intervention groups that receive PITCH training at period 2 or the control groups that receives PITCH training at period 3. All participants are monitored throughout the SW-CRT and outcomes for all participants are assessed at three time periods: period 1 (baseline), period 2 (at 6 months), and period 3 (at 12 months). See Fig. 1.

**Fig. 1 Fig1:**
[figure not shown]
Stepped-wedge schematic for the PITCH study. Each cell represents a data collection point. The PITCH intervention is introduced sequentially in groups of 8 clusters (blue shaded cells)

### Trial setting

This multi-site national study will be conducted in three Australian states (Victoria [VIC], New South Wales [NSW], and South Australia [SA]). The lead organisation for this study is the National Ageing Research Institute, in collaboration with the University of Sydney and seven partner home care service providers, representing the not for profit home care sector in the three most populous States of Australia: Australian Unity (VIC and NSW), Royal Freemasons (VIC), Villa Maria Catholic Homes (VIC), Benetas (VIC), Whiddon (NSW), and Helping Hand and ACH (SA). At least one cluster from each home care provider will participate in the study. These clusters are service regions as per the organisational structure of the provider or are pre-defined by geographical area. Minimising contamination and home care workforce size are strong considerations when pre-defining clusters. This study used the SPIRIT reporting guidelines [15]. Details of the study design are shown in Fig. 2.

**Fig. 2 Fig2:**
[figure not shown]
Schedule of enrolments, interventions and assessment. SCIDS, Sense of Competency in Dementia Care Staff; DKAS, Dementia Knowledge Assessment Scale; DAS, Dementia Attitudes Scale; SDCS, Strain in Dementia Care Scale; ASCOT SCT4, Adult Social Care Outcomes Toolkit SCT4; NPI, Neuropsychiatric Inventory; DAD, Disability Assessment for Dementia Scale; CER-Draft, Consumer Experience Report Draft version; EQ-5D-5L, Euroqol 5 Dimensions 5 Levels; ICECAP-O, ICEpop CAPability for Older people; RUD Lite, Resource Utilization in Dementia Lite version; ZBI, Zarit Burden Interview; DRS, Dyadic Relationship Scale; RUDAS, Rowland University Dementia Assessment Scale. Routine data includes demographic-, medical-, and care-related documentation providing at screening or from the home care providers during the trial. Asterisk indicates HCW measure; pound sign indicates client measure (self-report or proxy); dagger symbol indicates family carer measure

## Participant and eligibility criteria

### Recruitment

For this study, there are multiple levels of participants: clients living with dementia, their family carers, and HCWs from partner home care providers. Home care providers will be instructed not to recruit clients on behalf of the research team, but they may identify potentially suitable clients and inform them about the study. If the clients or their family carers agree to be contacted, a research staff member approaches them to discuss the study. Whilst family carers are also approached to participate, they are only enrolled into the study if the client is also participating. Home care providers facilitate HCW recruitment via advertisements and internal staff communication. Letters of invitation with study information will be sent to potential HCWs, and those who are interested are asked to contact the research team.

### Identification of participants and eligibility

#### Inclusion criteria

HCWs: Any frontline adult (aged 18+ years) HCW who provides services for a client living with dementia who is receiving home care services funded by the government Home Care Packages Program or Commonwealth Home Support Programme.

Clients: Adult with a diagnosis of dementia (of any type and stage) or screen positive on the Noticeable Problems Checklist [16] and receiving home care services funded by the Australian Government Home Care Packages Program or Commonwealth Home Support Programme. The Noticeable Problems Checklist is used instead of a formal cognitive screen to minimise client distress and so service providers can refer potentially eligible participants.

Family carers: Adult who cares for a participating client in this study. The family carer must know the client well and spend a minimum of 6 h with the client each week.

#### Exclusion criteria

Clients: If (in the opinion of the service provider) their death is likely within the next 6 months due to the course of chronic disease (e.g. palliative), if they (or their family carers) have plans to move into an aged care facility within the next 6 months, or if they (or their family carers) have plans to change home care providers within the next 6 months.

Family carers: If they lack the ability to provide informed consent.

### Intervention Procedures

The PITCH training programme was co-designed with HCWs and managers, people with dementia and their family carers [see [17, 18] for further details on the development of the PITCH program]. The content was specifically tailored for relevance to paid HCWs who provide services to clients living with dementia. The programme includes the following content: key information about dementia and its presentations and impact on daily living, practical strategies for effective communication with clients living with dementia and their family carers, person-centred care, understanding triggers for changed behaviours and effective responses, as well as strategies for staff self-care.

The programme was originally designed as a face-to-face training program. In response to government guidelines and restrictions due to the COVID-19 pandemic, PITCH training has also been adapted for online delivery. The face-to-face programme is conducted as two half-day workshops (total length is 7 h including breaks), and the online programme is delivered across three 2-h sessions (total 6 h), with similar programme content across the two modes of delivery. In the training, HCWs are provided with a workbook and encouraged to actively participate in group discussion through case studies and role modelling to provide experiential learning. During the trial, HCWs will be able to attend the PITCH training and complete the outcome measures at all periods as part of their work time, with backfilling of their shift funded by the study. HCWs attendance will be noted by the research team and reported back to site managers. In discussion with site managers, training sessions will be scheduled to maximise HCW attendance. Managers will promote the sessions and encourage attendance, though PITCH training will not be compulsory. Implementing PITCH will not require alteration to usual care pathways for dementia care and these will continue for both trial arms.

#### Trial conduct

Day-to-day trial conduct will be monitored by NARI’s project research team who will meet fortnightly. A project advisory group (PAG) (including members living with dementia and informal carers) will meet quarterly to provide guidance and input into the conduct of all stages of the project and ensure that the project is carried out in a manner that respects all involved. A project management group (PMG), consisting of chief investigators and associate investigators of the project, will also meet quarterly for additional trial oversight. Modifications to the protocol will be submitted to the Human Research Ethics Committees (HRECs) to review, which will then be reported to project advisory and management groups.

#### Criteria for discontinuing or modifying intervention for allocated intervention

HCWs: The intervention will be discontinued if they are no longer employees of a participating provider.

Clients and family carers: The intervention will be discontinued if the client stops receiving care from a participating provider.

There will be no other special criteria for discontinuing or modifying allocated interventions.

### Outcome measures

Measures are obtained at three time-points (periods 1, 2, and 3: baseline, 6 months, and 12 months respectively). See Fig. 2 for the timing of outcome assessments.

#### Data collection plan

The research team who will collect data will be fully trained prior to data collection. A data monitoring process will also be implemented. HCW measures will be self-administered, whilst client and informal carer measures will be measured by the research team.

### Primary outcome

Sense of competence has emerged as an important clinical concept [19]. The primary outcome of this study is HCWs’ sense of competency in providing care services to clients with dementia living at home as assessed by the Sense of Competency in Dementia Care Staff (SCIDS) [20] self-reported questionnaire. SCIDS has 17 items that measure four domains: professionalism, building relationships, care challenges, and sustaining personhood. SCIDS has been shown to have adequate psychometric properties [19], including responsiveness to dementia training across different community settings [21].

### Secondary outcomes

HCWs will be assessed on their general knowledge of dementia using the Dementia Knowledge Assessment Scale (DKAS) [22]. Their attitudes towards people living with dementia will be assessed using the Dementia Attitudes Scale (DAS) [23], though the scale has been modified to change the term ‘ADRD’ (Alzheimer’s disease and related disorders) to ‘dementia’ for consistency with the other measures used. The stress experienced by HCWs in providing dementia care will be assessed using the Strain in Dementia Care Scale (SDCS) [24].

For clients living with dementia, their sense of control over daily personal life and social activities will be assessed by HCWs or family carers, using the Adult Social Care Outcomes Toolkit ASCOT-SCT4 [25]. Information about client experiences when receiving home care will be assessed using the Consumer Experience Report Pilot Draft (CER-Draft, new scale) [26]. The health-related quality of life of clients will be assessed using the Dementia Quality of Life (DEMQOL) [27] or proxy version (DEMQOL-Proxy). Family carers rate the presence and severity of client neuropsychiatric symptoms, as well as the level of caregiver distress resulting from the symptoms, using the Neuropsychiatric Inventory (NPI-12) [28]. Functional daily activities of people with dementia in community dwelling will be assessed using the Disability Assessment for Dementia Scale (DAD) [29]. Caregiver personal and role strain will be assessed by the family carer using the Zarit Burden Interview (ZBI) self-report scale [30].

By improving staff dementia knowledge, attitudes, confidence, and competence, it will likely improve the overall quality of dementia care provided by HCWs, with foreseeable client ability to remain independently living at home.

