### Blinding

HCWs are unblinded during the study. The clients and family carers are told that their HCWs will receive the PITCH training but are not informed when training has occurred. Clients and family carers are not provided with information about the training content. HCWs are encouraged to not discuss the training with their clients.

Research staff liaising with the home care providers and the training team from the home care providers remain unblinded throughout the project. Research assistants collecting outcome measures during client, family carer, and HCW assessments are blinded to the randomisation condition.

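### ASCOT-SCT4, a client secondary outcome, may be rated by the unblinded home care workers who receive the training, so a change in their scoring would be confounded with the intervention effect

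*Protocol article*

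**What the plan says.** The Secondary outcomes section introduces the measure as a client outcome: "For clients living with dementia, their sense of control over daily personal life and social activities". It then names two possible kinds of rater: these "will be assessed by HCWs or family carers, using the Adult Social Care Outcomes Toolkit ASCOT-SCT4".

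Other sections bear on those raters:

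- Trial design: "This SW-CRT is an interventional study for HCWs as they receive PITCH training". Clients and family carers receive no direct intervention.
- Blinding, on the workers: "HCWs are unblinded during the study".
- Blinding, on clients and family carers: they "are told that their HCWs will receive the PITCH training but are not informed when training has occurred".
- Blinding, on data collection: "Research assistants collecting outcome measures during client, family carer, and HCW assessments are blinded to the randomisation condition".
- Data collection plan: "HCW measures will be self-administered, whilst client and informal carer measures will be measured by the research team".
- Statistics and data analysis: client outcomes go into linear or generalised linear mixed models with time and intervention as fixed effects and cluster and participant as random effects. No rater term is stated.

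**The concern.** For this outcome the person scoring the client can be the person who was trained, and who knows it. PITCH sets out to change HCWs' knowledge, attitudes and sense of competence, and its content includes person-centred care. A trained worker may therefore judge a client's control over daily life by a different standard, even when nothing has changed for the client. Such a shift would coincide with the move from control to intervention, so the analysis could not separate it from a real change.

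The trial's second research question is whether training HCWs indirectly improves outcomes for clients and family carers. A client score supplied by the trainees is weak evidence on that question. The protocol already has a better-protected informant in the family carer, whom the same section names as the rater for the NPI-12 and the Zarit Burden Interview. ASCOT-SCT4 is the only client outcome in that section for which HCWs are named as raters.

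**Working it through.** The article states no figure on this point, so there is none to reproduce. The check is first of the text, then an illustration.

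**Text, set side by side**

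1. Rater: HCW or family carer (Secondary outcomes).
2. HCW: receives the training (Trial design) and is unblinded (Blinding).
3. Family carer: knows that training will happen but is not told when (Blinding). This protection is partial, but an HCW has none.
4. Blinded research assistants collect the data (Blinding). That protects against bias from the collector. It cannot blind an HCW who supplies the score.
5. Model: time and intervention only as fixed effects (Statistics and data analysis). A scoring shift that begins with training is aligned with the intervention term. Neither the time effect nor the random effects for cluster and participant remove it.

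**Illustration of size**

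Let h be the share of forms rated by HCWs and b the shift in HCW scoring after training, in SD units. With no true client effect, the spurious effect is h × b. The article gives neither quantity; both ranges are assumptions.

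- Low: h = 0.25, b = 0.2: 0.25 × 0.2 = 0.05 SD.
- Middle: h = 0.50, b = 0.3: 0.50 × 0.3 = 0.15 SD.
- High: h = 0.50, b = 0.4: 0.50 × 0.4 = 0.20 SD.
- If h = 0 or b = 0, the bias is zero.

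To see what this could do to a test, take a simple two-group comparison at 6 months:

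- About 108 clients (Sample size), split 54 v 54.
- 18 clusters (Abstract), so 108/18 = 6 clients per cluster.
- Design effect DE = 1 + (6 − 1) × ICC, with an assumed ICC of 0.05: DE = 1.25.
- SE = √(2/54 × 1.25) = 0.215 SD.
- False-positive rate = P(|Z| > 1.96), where Z has mean h × b / SE.

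| Spurious effect | ICC 0 | ICC 0.05 | ICC 0.10 |
|---|---|---|---|
| 0.05 SD | 5.8% | 5.6% | 5.5% |
| 0.15 SD | 12.2% | 10.7% | 9.8% |
| 0.20 SD | 18.0% | 15.3% | 13.6% |

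The nominal rate is 5%. With the 12 clusters used in the Sample size section, cluster size would be 108/12 = 9 and DE at ICC 0.05 would be 1 + 8 × 0.05 = 1.40. This lies inside the range of 1 to 1.5 that the table covers. The calculation simplifies the three-period design, does not model a change of rater between periods, and is no estimate for this trial.

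**Cost of relying on carers**

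The Sample size section expects about 108 clients and about 108 family carers. On those planning figures, few clients would lack a participating carer.

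**The case against.** The strongest reply is that the word *or* may already mean what the fix proposes. Neither the client eligibility criteria nor the Recruitment section requires a participating carer, so HCW rating could be the fallback where there is none. The article condenses a fuller protocol, and a rule for choosing the rater may stand there or in an analysis plan. This stands as far as it goes: a reader might infer that raters are used interchangeably or may switch between periods, but the article's silence does not show that. What remains is what the text does state, namely that HCW ratings are admitted for this outcome. A fallback rule would reduce their share without removing the problem.

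A reader might also infer that the Data collection plan flatly contradicts the Secondary outcomes section, since client measures "whilst client and informal carer measures will be measured by the research team". The documents do not support that. One sentence can be about who administers a measure and the other about who supplies the answers; carer-rated scales are subject to the same two statements. It is a tension: the article does not say how an HCW-supplied client rating is taken.

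Four further limits are fair:

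- The bias need not favour PITCH. Training could make HCWs more critical and hide a benefit.
- Assessments are six-monthly, and nothing shows that the rating HCW has only recently been trained or is judging their own care of that client.
- Carers are not fully protected: they know that training is coming, and HCWs are only encouraged not to discuss it.
- At the low end of the illustration, the false-positive rate hardly moves from 5%.

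**Conclusion.** The point holds on the stated text. An unblinded recipient of the training may rate a client secondary outcome, blinded data collection does not cure this, and the stated model would attribute a training-related scoring shift to the intervention. It is a risk of bias in either direction, not a demonstrated bias.

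Its size cannot be derived from the article. The range of 0.05–0.20 SD rests wholly on an assumed HCW-rated share of 25–50% and an assumed shift of 0.2–0.4 SD. It would be wrong to read it as an expected inflation of benefit.

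The scope is narrow. A reader might extend the point to client effects in general, but no other client outcome is stated to be HCW-rated. The primary outcome, SCIDS, is an HCW self-report by design and is not affected. The correction is still worth making because it is cheap and bears directly on the trial's second research question.

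**What to change.** - **Secondary outcomes:** state that the family-carer rating is the main ASCOT-SCT4 score wherever a carer participates, and that HCW ratings are used only for clients without a participating carer. Keep the same rater type for a client across periods where this is still possible; the trial was under way in September 2021 with completion expected in April 2022, so for forms already collected it may not be.
- **Data:** record rater type on every ASCOT-SCT4 form, including those already collected.
- **Analysis:** make the carer-rated set the main ASCOT-SCT4 analysis, report HCW-rated data separately as supportive, and add a sensitivity analysis with all raters.
- **Data collection plan:** say how a client rating supplied by an HCW is collected, so that it reads consistently with the Secondary outcomes section.

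The cost is wording and one variable, with no extra staff. The downside is that clients without a participating carer leave the main ASCOT-SCT4 analysis. They are a selected group, though probably a small one on the planned numbers, and the all-rater sensitivity analysis keeps them in view.
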